### 1.5 Need for new treatment options

The large individual and economic burden upon the health care system demands fundamental changes in the treatment and prevention of urolithiasis. The recommended lifestyle changes including increasing fluid intake, weight loss, reduction of sodium consumption, and increase of potassium-rich foods are difficult to adhere to and often only of short benefit. For instance, even under the conditions of an RCT where intensive coaching was applied to increase water intake, the treatment effect was mild with an increase of urinary volume of 0.6 L/day in the treatment group [77]. Similar findings have been observed in pragmatic RCTs aiming at weight reduction through structured coaching on behavioral changes [78].

The current drug treatment options are limited by tolerance, side effects, and low efficacy of therapy. Therapy with HCT has been shown to have no benefit compared with the placebo group in the frequency of events nor in the risk of reoccurrence independently of the dosage. Additional to the lack of efficacy in this specific indication it should be emphasized that long-term therapy with HCT increases the risk of melanoma and non-melanoma skin cancer in non-Asian countries, and regular screening for this skin cancer is necessary [79]. Due to this fact, HCT is no longer recommended by the guidelines of 2023 of the German Urology Association as prevention therapy for recurrent kidney stone patients. Alkaline citrate supplementation may provide beneficial effects in hypocitraturia, but its application is limited by reduced gastrointestinal tolerance, leading to treatment discontinuation in a large proportion of patients.

In summary, in the current situation, there exists no relevant and effective therapy options for the mass of patients with a high risk of reoccurrence based on a significantly increased risk of and/ or an increased number of urolithiasis events within the past years. Further research is needed to identify at least one option for this specific group of patients. If successful, decreasing the frequency of recurrent nephrolithiasis would increase the quality of life for these patients and reduce morbidity and healthcare-related costs.

## 2. Materials and methods

### 2.1 Study aim and perspective

In summary, further research is needed to confirm the assumption that Dapagliflozin can reduce oxalate and/or calcium excretion and in further consequence reduce the risk and frequency of urolithiasis. Moreover, the real pathophysiological effects are unknown, which is why we also include preliminary and in-depth metabolomics analysis of blood and urine- to narrow down potential biochemical pathways.

As one of the most common diseases globally, urolithiasis has a prevalence of 1% to 20% combined with high comorbidity and treatment costs [1,2]; the relapse rate within the first 10 years after initial treatment is about 60% [3]. After the first episode of kidney stones lifestyle modification is recommended to every patient. Supplementation and pharmaceuticals are recommended to be reserved for recurrent episodes. High-risk patients need preventive therapy adjusted to their metabolic abnormalities [18–21,61].

The evidence for current stone-preventing therapies based upon the determining stone composition or on biochemistry measures is low. Furthermore, especially in high-risk patients, the outcome of the above-mentioned therapies varies widely and has a significant failure rate [21,62]. Recent studies focusing on urolithiasis event-rates however showed a reduction of the frequency [68, 69]. In the case that dapagliflozin decreases the incidence of urolithiasis regardless of underlying comorbid disease a serious alternative to repetitive surgical treatment can be offered to affected patients. Especially hyperoxaluric patients will benefit from the new case application of dapagliflozin concerning reduced urolithiasis risk.

### 2.2 Trial design

*Study type:* Pharmacological randomized cross-over single-center study

Our study will be the first one prospectively targeting the effect of dapagliflozin on urolithiasis and the urinary compounds playing a role in its development we chose a two-part design to target relevant problems: Since no comparable, prospective trials in humans have been performed there is no data about the expected effect size. Therefore, the upstream exploratory phase will be performed to generate prospective data that will be the base of the sample size calculation of the main trial. (see 2.3 Sample size calculation).

#### 2.2.1 Exploratory phase.

The exploratory phase will focus on metabolomic analyses to identify the effects of dapagliflozin therapy in humans on the urine composition respectively electrolytes and small molecules that may interfere with the urolithiasis frequency such as oxalate, calcium, magnesium, citrate, and uric acid.

Therefore, one group of 22 participants with a diagnosed cardiomyopathy and/or diabetes Mellitus and indication for dapagliflozin will get a daily oral administration of 10mg dapagliflozin combined with regular blood- and urine test to generate data for the calculation of the effect size. Furthermore, we hope to gain more information about the pharmacologic mechanisms of how dapagliflozin modifies the frequency of urolithiasis events in humans as it has been shown in earlier studies [64,68,69].

The SPIRIT-Study workflow and assessment timeline with primary and secondary endpoints have been presented in Fig 1 and S1. Table.

**Fig 1 pone.0322034.g001:**
[figure not shown]
SPIRIT-Study Workflow and Assessment Timeline with Primary and Secondary Endpoints.

#### 2.2.2 Randomized controlled trial.

The second part, the main trial will also be a randomized cross-over single-center study in patients with a high risk of urolithiasis reoccurrence to show if dapagliflozin can modify the urine composition in hyperoxaluric patients with a high stone-forming risk. After a recalculation of the sample size based on the findings of the exploratory phase screenings of potential participants will run to gain the population needed for this trial section.

We hope to demonstrate that dapagliflozin is a new therapy option for high-risk stone formers with no known secondary causes. Participants eligible for the main trial must meet two key criteria: first, they must be selected from a group of patients with similar clinical profiles, specifically those classified as high-risk stone formers who have experienced a significantly increased frequency or severity of urolithiasis events in recent years. Second, they must not have any identifiable secondary causes for these events, such as known metabolic disorders, anatomical abnormalities, or medications known to predispose to stone formation (see 2.4 Trial participants).

After the end of the main trial, the participants of the main trial will be offered to be included in a follow-up trial. The participants will continue to get a daily oral dosage of 10mg dapagliflozin for a period of up to two years. By that, we would like to demonstrate the effect of dapagliflozin on the urolithiasis event rate in humans in the first prospective trial even if short-term or metabolomic data of the first two study phases will gain no new information about the pathophysiology and the pharmacologic pathways behind this disease.

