**Methods:**

This study will proceed in two phases: an exploratory phase and a randomized controlled phase. In the exploratory phase, 22 participants with indications for dapagliflozin treatment will be evaluated before and after treatment initiation to ascertain the concrete effect size regarding oxalate and calcium-sparing effects. This data will inform the calculation of the study sample size (ranging from 17 to 104 participants) to include high-risk calcium oxalate kidney stone formers in a randomized controlled crossover study design. Treatment phases—one with dapagliflozin and one with placebo—will alternate with wash-out phases involving placebo. The primary outcome is the reduction of oxalate excretion in 24-hour urine samples compared to baseline values after 8 weeks of therapy. Secondary objectives include analysing effects on kidney function, the frequency of urolithiasis, and treatment tolerance. Additionally, in-depth metabolomics analyses will explore pathophysiological pathways during treatment. Investigators, patients, and research staff will be blinded to the randomization list. This study was initially registered under EudraCT (Nr:2022-000994-13) and has been transitioned to CTIS (Nr: 2024-519371-25-00) to comply with EU Regulation 536/2014, ensuring streamlined management and transparency.

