#### 1.3.1 Calcium-oxalate stones and recurrence rates.

Urolithiasis is one of the most common diseases globally with high comorbidity and treatment costs with a prevalence from 1% to 20% [1, 2]. The relapse rate of calcium-oxalate stones within the first 5 years after initial treatment is about 40% and increases to 75% in the first 20 years. Several studies demonstrated a recurrence rate between 43–80% at three years among a cohort of subjects with a history of recurrent calcium stone formation [53–60].

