#### 2.4.3 Inclusion criteria.

The patient informed about the study procedures as described and documented by the signed consent formAge >18 yearsCalcium-oxalate stone formers with a high risk of reoccurrence are defined as:A. At least two symptomatic or surgically treated kidney stones within the last 10 years; In particular; patients who have experienced at least two distinct symptomatic or surgically treated kidney stone episodes within the last 10 years, confirmed by imaging or surgical retrieval. Each episode must be separated by a period where the patient was either stone-free or had no symptoms, as verified by clinical evaluation or imaging to exclude the possibility of residual fragments from previous procedures, and/orB. Single stone kidney formers with risk factors include:a. Positive medical family history on kidney stone formations of at least one blood-related relative in the first degree or at least two blood-related relatives in the second degree and/ orb. The onset of kidney stone formations within the third life decade or earlier and/ orc. Metabolic syndrome and/ ord. Obesity (BMI ≥ 30 kg/m²)

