#### 2.6.2 Main trial phase.

The main trial will start with wash-out phase I. All patients will receive blood- and 24-hour-urine screenings in week 6 (respectively week 12 overall) to get baseline data. In preparation for the treatment phase I all participants will receive a daily oral placebo administration over the whole period and will be randomized in two groups.

In week 13 the treatment phase I will start and group 1 will receive oral therapy with 10mg of dapagliflozin while group 2 will get an oral placebo administration daily; the treatment response will be evaluated by blood- and urine test after 4 weeks of therapy (respectively week 16 overall) and in the beginning of in washout phase II (respectively week 21 overall). The same test as before will be performed after 6 weeks (respectively week 26 overall) to gain baseline data for treatment phase II. In preparation for the treatment phase II, all participants will receive a daily oral placebo administration. will receive a daily oral placebo administration.

In the end, we will perform treatment phase II with an oral administration of 10mg of dapagliflozin for group 2 and daily placebos for group 1. The treatment response will be evaluated by blood- and urine tests after 4 weeks of therapy (respectively week 30 overall). Finally, the same tests as before will be performed in wash-out phase III in weeks 1 and 6 (respectively weeks 35 and 40 overall). This way we will get data of the non-therapy periods and of the outcome that will be caused by the dapagliflozin therapy. For each patient, a comparison will be made between the excretion of the electrolytes and molecules of the primary and secondary endpoints under dapagliflozin therapy vs. oral placebo administration.

Throughout the whole study procedure, all participants will be advised to follow dietary instructions as recommended in the urolithiasis guidelines of 2023 [62]. The requested measures will include a balanced diet including a high ratio of vegetables and fibers, a low-fat diet, a calcium intake of about 1.0 to 1.2g per day, a reduced intake of salt up to a maximum of 4.0 to 5.0g per day and an intake of animal proteins of 0.8 to 1.0g per kg per day may reduce stone development risk. Furthermore, patients are strongly advised to not lose or gain weight tremendously throughout the trial process so that the date will be comparable over the whole trial period.

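### The opt-in follow-up on dapagliflozin names no concurrent control, so it cannot demonstrate an effect on stone event rate and should be described as uncontrolled and descriptive

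*Protocol article*

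**What the plan says.** Section 2.2.2 says that, after the main trial, "the participants of the main trial will be offered to be included in a follow-up trial". It gives that follow-up a single regimen: "The participants will continue to get a daily oral dosage of 10mg dapagliflozin for a period of up to two years". The next sentence states the purpose: "By that, we would like to demonstrate the effect of dapagliflozin on the urolithiasis event rate in humans in the first prospective trial". The same sentence adds that this holds even if the first two phases bring nothing new on mechanism, so the follow-up is meant to carry the event-rate aim by itself.

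The population is selected on stone history. Section 2.2.2 describes main-trial participants as "specifically those classified as high-risk stone formers who have experienced a significantly increased frequency or severity of urolithiasis events in recent years". Section 2.4.3 admits either "At least two symptomatic or surgically treated kidney stones within the last 10 years" (criterion A, with separated episodes) or a single stone with risk factors (criterion B).

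The follow-up does not appear in the hypotheses and endpoints (2.5), the schedule (2.6), the statistics (3.1) or the work packages (3.3). The only controlled comparison of stone events in the document lies inside the crossover: a secondary objective (2.5.3), compared between treatments by a McNemar test (3.1).

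**The concern.** An effect on event rate is a statement about what would have happened to these patients without the drug. If everyone in a phase takes the drug, that phase cannot supply the missing half of the comparison. The text links the aim directly to the single-regimen design, so this is a mismatch between a stated aim and a stated design, not a detail left to another document.

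At stake is an unsupported claim of stone prevention. A lower event rate than before entry could reflect the drug, the way patients were selected, dietary advice, or who chose to continue. The design offers no means of separating these.

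**Working it through.** The plan gives no sample size, target rate, event count or analysis for the follow-up, so there is no figure of its own to reproduce. The check is whether any available comparator would support the aim.

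**1. Is there an internal control?** Section 2.6.2 gives dapagliflozin to group 1 in treatment phase I and to group 2 in treatment phase II. By the end of the crossover both sequences have been exposed, so the original randomisation leaves no unexposed group. No re-randomisation is stated, and entry is by acceptance of an offer.

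**2. Comparator A: the patients' own history.** Selection on past events makes a later fall plausible without any drug effect. As an illustration only, a gamma-Poisson model was simulated with a population mean of 0.036 to 0.2 events per year and shape 0.5 to 2. These parameters are assumptions, not figures from the document. Patients selected for at least two events in 10 years then have a later rate of 0.29 to 0.88 times their qualifying rate, an apparent fall of 12% to 71%. The cited hazard ratio of 0.68 (section 1.4.4) is a fall of 32%, inside that range. The model shows what is possible; it does not estimate the bias in this trial.

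**3. Comparator B: placebo and wash-out time in the main trial.** The abstract gives a main-trial size "ranging from 17 to 104 participants". At the upper end, with no losses:
- One 8-week placebo period: 104 × 8/52 = 16 person-years.
- Adding three 6-week wash-outs (26 weeks in all): 104 × 26/52 = 52 person-years.
- At 0.053 per year: 16 × 0.053 = 0.8 events, or 52 × 0.053 = 2.8.
- At 0.187 per year (derived in step 4): 16 × 0.187 = 3.0 events, or 52 × 0.187 = 9.7.
- At 0.536 per year (also step 4): 16 × 0.536 = 8.6 events, or 52 × 0.536 = 27.9.

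This time is post-entry and in the same patients, but it is earlier, short, and partly follows dapagliflozin.

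**4. Comparator C: published rates in the document.** Assuming constant hazard h, the two-year risk is 1 − exp(−2h).

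| Source | h per year | Two-year risk |
|---|---|---|
| 53 per 1,000 person-years (1.4.4) | 0.053 | 10% |
| 40% at 5 years (1.3.1) | −ln(0.60)/5 = 0.102 | 18% |
| 43% at 3 years (1.3.1) | −ln(0.57)/3 = 0.187 | 31% |
| 80% at 3 years (1.3.1) | −ln(0.20)/3 = 0.536 | 66% |

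The last two rows come from this statement: "Several studies demonstrated a recurrence rate between 43–80% at three years". The hazards differ by a factor of 0.536/0.053, about 10. Suppose the untreated risk were 31% and the drug truly had a hazard ratio of 0.68. The observed two-year risk would be 1 − exp(−0.68 × 2 × 0.187) = 22%: a benefit against the 31% and 66% rows, and an excess against the 10% and 18% rows.

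**5. Precision.** With 104 participants for two years there are 208 person-years. At 53 per 1,000 that gives 11 events, with an exact 95% interval of about 26 to 95 per 1,000, which contains both registry rates (36 and 53). At the lower end of the planned size, 17 × 2 × 0.053 = 1.8 events.

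**6. Would a control arm alone be enough?** For a hazard ratio of 0.68 at two-sided 5%, Schoenfeld's formula needs 283 events for 90% power and 212 for 80%. Expected events among 104 participants over two years are 208 × 0.036 = 7 and 208 × 0.053 = 11 at the registry rates, and 208 × 0.187 = 39 to 208 × 0.536 = 112 at the three-year recurrence figures. All fall short.

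**The case against.** The strongest reply is that the follow-up is a separate trial whose own protocol is not shown. It lies outside the endpoints and schedule given here, and main-phase data collection is due to end on 01.07.2026 (3.3.1), which leaves no room for two further years. A comparator could be defined elsewhere. This stands as a limit on scope and supports treating the point as one of wording. It does not remove the point, because this article fixes one regimen and builds the causal aim on it.

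Several stronger readings are tempting and are not supported:

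- A reader might infer that a fall in event rate is to be expected even with an inactive drug. The documents do not show this. The minimum rate under criterion A is 2/10 = 0.2 per year, and the three-year recurrence figures imply 0.187 to 0.536 per year, mostly not lower. Criterion A also requires separated episodes, and criterion B admits single-stone formers. Regression to the mean is plausible, but its size is unknown.
- A reader might infer that history and published rates are the only comparators. The main trial's placebo and wash-out periods are a third. They are post-entry and under the same dietary advice, so they escape part of the bias, but they are short and non-concurrent.
- A reader might infer that any result between 10% and 66% could be called benefit or harm at will. That fails at the ends: 10% cannot be harm and 66% cannot be benefit against these figures. The figures also pool different populations, including a GLP-1 receptor agonist cohort, and the document proposes none of them as a comparator.
- A reader might treat dietary advice as a certain confounder. Section 2.6.2 says that "all participants will be advised to follow dietary instructions as recommended in the urolithiasis guidelines of 2023", but this concerns the main trial, and lifestyle advice is already recommended after a first stone (1.3.2).
- A reader might conclude that the trial's main claim is undermined. The confirmatory endpoint is oxalate excretion, and the Discussion does not mention the follow-up.

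None of these replies supplies a valid control.

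**Conclusion.** The point holds in a limited form. As described in section 2.2.2, the follow-up is an opt-in phase on a single regimen with no concurrent control named, in patients selected for past stones and already exposed to the drug. It cannot demonstrate an effect on stone event rate.

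This conclusion rests on the missing comparator, not on the illustrative figures. The 10% to 66% spread depends on constant hazard, which is rough: section 1.3.1 itself gives 40% at 5 years (0.102 per year) and 75% at 20 years (−ln(0.25)/20 = 0.069 per year). The 12% to 71% range depends on assumed model parameters. The event counts assume the largest planned sample with full follow-up.

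The consequence is confined to what the follow-up may conclude. The main trial's primary endpoint, sample size and analysis are not touched. The change should be made, because it costs little and prevents an unsupported prevention claim.

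**What to change.** In section 2.2.2, replace the stated aim with wording such as: *the follow-up will describe the stone event rate (with 95% CI), tolerability and adherence on dapagliflozin*. Add that the phase is uncontrolled, and that any before/after or historical comparison of event rate is exploratory and not evidence of efficacy.

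This is a text change only; the follow-up can run as planned. The cost is that the sponsor gives up an efficacy claim that the design cannot support. If a causal claim is wanted, it needs a concurrent randomised comparison with its own event-based sample size; by the arithmetic above, adding a control arm at the current size would not be enough.

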### 2.3 Sample size calculation

#### 2.3.1 Sample size calculation of the exploratory phase.

As mentioned above, no data exists about the effect of dapagliflozin on the oxalate and calcium 24-hour urine excretion. Given the observed decrease in urolithiasis event rates in previous studies [68,69] and findings from a rat model investigating the impact of SGLT-2 inhibitors on urolithiasis [69] we anticipate a 10%-50% reduction in 24-hour urinary excretion of oxalate and calcium compared to placebo. This expectation is supported by evidence suggesting that a 10% decrease in urinary excretion of calcium and oxalate is linked to a significant 8% reduction in the risk of recurrence [76]. We, therefore, expect a) the effect size of dapagliflozin to be a reduction of urinary excretion of lithogenic molecules between 15% and 25% reduction and b) subsequently to have a clinically relevant potential to lower the risk of urolithiasis reoccurrence.

The sample size calculation is based on our primary outcomes of the intraindividual comparisons. The sample size calculation based on a paired t-test was performed using G*Power Version 3.1.9.4. The significance level of two-sided testing was set to 0.025 to acknowledge the two primary endpoints [80]. We set the power to 90% and the alpha error to 5%. Due to no comparable data, we assume a standard deviation of 20% and a correlation between the intraindividual comparisons of 0.1. Based on the sample size models in Table 1. (assumed effect size of 25%, correlation between the groups of 0.1) we proclaim a group size of 18 participants plus an expected dropout rate of 4 so a total of 22 participants is reasonable.

**Table 1 pone.0322034.t001:** potential group size calculations based on earlier findings.

Mean difference	Mean ± SD group 1	Mean ± SD group 2	Group size	Group size + 20% dropout
10%	1.0 ± 0.2	1.1 ± 0.22	86	104
15%	1.0 ± 0.2	1.15 ± 0.23	42	51
20%	1.0 ± 0.2	1.2 ± 0.24	26	32
25%	1.0 ± 0.2	1.25 ± 0.25	18	22
30%	1.0 ± 0.2	1.3 ± 0.26	14	17

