#### 2.3.2 Sample size calculation of the main trial.

Under the Null hypothesis that dapagliflozin reduces the oxalate concentration in the 24h urine by the effect shown in the exploratory phase compared to the baseline value, we will re-calculate the needed number of participants to demonstrate this effect with 90% power and a 5% alpha error in a two-sided test. In expectation of dropouts an additional number of patients of 20% of the calculated sample size will be added to the study collective.

The sample size will be calculated by using G*Power Version 3.1.9.4 with the following parameters: two-sided t-test, expected effect size 25%; significance level = 0.025; power = 0.9; alpha error 5% dropout rate 20%.

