## 3. Statistics

### 3.1 Statistical analysis

We plan to perform statistical analysis conforming to the standard methodology. Categorized data will be presented as absolute count and relative frequencies. Continuous data will be reported as mean and standard deviation in case of normal distribution and as median and inter-quartile range (IQR) in case of a non-normal distribution. Two-sided tests are considered to be significant with a p-value <0.05.

Analyses of continuous variables will be performed using parametric and non-parametric tests (paired t-test/ Mann-Whitney-U-test). The primary endpoint is confirmatory and is the reduction of oxalate in the Verum vs. Placebophase, i.e., Dapaglifozine vs. placebo which will be compared with a two sided-t-test. Intergroup comparisons (Dapaglifozine vs placebo) will be performed by an ANOVA for a crossover design on the group of patients who went through all trial phases and corrected with Bonferroni post-hoc Tests for multiple testing. Frequencies of urolithiasis will be tested with the x²-test, a in comparison of both treatments by the McNemar-Test. Correlations between variables will be performed using Pearson or Spearman coefficients.

Findings will be corrected for multiple testing using the Tukey method if the statistical analysis is performed with a one-way ANOVA or with the Shaffer correction if the statistical analysis is performed with a Kruskal-Wallis test. All other statistical tests will be corrected using the Bonferroni-Holm method.

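### Table 1's group sizes were computed at two-sided alpha 0.05, not the stated 0.025, and the alpha for the main-trial recalculation is stated two ways

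*Protocol article*

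**What the plan says.** Section 2.3.1 gives the design inputs for the exploratory phase. The test: "The sample size calculation based on a paired t-test was performed using G*Power Version 3.1.9.4". The level: "The significance level of two-sided testing was set to 0.025 to acknowledge the two primary endpoints". The next sentence reads "We set the power to 90% and the alpha error to 5" per cent. The variability: "we assume a standard deviation of 20% and a correlation between the intraindividual comparisons of 0.1". The expected effect is "a reduction of urinary excretion of lithogenic molecules between 15% and 25% reduction".

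Table 1 lists five scenarios, from 1.0 ± 0.2 versus 1.1 ± 0.22 (labelled 10%) to 1.0 ± 0.2 versus 1.3 ± 0.26 (labelled 30%). The group sizes are 86/42/26/18/14, and 104/51/32/22/17 with dropout. From the 25% row the authors conclude "we proclaim a group size of 18 participants plus an expected dropout rate of 4 so a total of 22 participants is reasonable".

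Section 2.3.2 lists the inputs for the main-trial recalculation, among them "significance level = 0.025; power = 0.9; alpha error 5% dropout rate 20" per cent. The text just before that list asks for a 5% alpha error in a two-sided test. Section 2.5.3 names one primary endpoint, urinary oxalate, and section 2.5.4 places calcium among the secondary endpoints. Section 3.1 sets the analysis rule: "Two-sided tests are considered to be significant with a p-value <0.05".

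**The concern.** If 0.025 is the per-endpoint level for two primary endpoints, the sample sizes should have been computed at 0.025. If they were not, the table claims a multiplicity adjustment that it does not contain, and its 90% power is not the power at the stated level.

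The same pair of alphas then reappears in the instructions for the main trial, where the reason for 0.025 is gone. That recalculation has not been run, so whoever runs it must choose between two levels. Under Table 1's assumptions the choice moves the group size from 18 to 21 in the 25% row and from 86 to 102 in the 10% row.

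The table's means also run upwards from 1.0 although the planned effect is a fall, so the percentage labels do not describe the reduction being powered. The 22 participants and the abstract's range of 17 to 104 both come from this table.

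**Working it through.** **Inputs.** All are from section 2.3.1 and Table 1: paired t-test, two-sided, power 0.90, r = 0.1, and the means and SDs of each row.

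**Formulas.** SD of the difference = √(s₁² + s₂² − 2·r·s₁·s₂). Standardised effect d = mean difference / SD of the difference. Power comes from the noncentral t distribution with n − 1 degrees of freedom and noncentrality d·√n. The group size is the smallest n with power of at least 0.90.

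**Worked row (25%).** The SD of the difference is √(0.04 + 0.0625 − 2·0.1·0.2·0.25) = √0.0925 = 0.3041, so d = 0.25/0.3041 = 0.822. At n = 18 the power is 90.7% at two-sided 0.05 and 83.7% at two-sided 0.025.

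**Step 1: reproduce the table.**

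| Row | d | Printed n | n at 0.05 | n at 0.025 | Power of printed n at 0.025 |
|---|---|---|---|---|---|
| 10% | 0.354 | 86 | 86 | 102 | 84.1% |
| 15% | 0.518 | 42 | 42 | 49 | 84.5% |
| 20% | 0.674 | 26 | 26 | 30 | 84.6% |
| 25% | 0.822 | 18 | 18 | 21 | 83.7% |
| 30% | 0.962 | 14 | 14 | 17 | 84.2% |

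All five rows match at 0.05 and none matches at 0.025. Other readings at 0.025 also fail to give the whole table:
- equal SDs of 0.2: 92/43/25/17/13
- normal approximation: 99/47/28/19/14
- unpaired test: 111/53/32/22/17
- r = 0: 113/54/33/23/18
- r = 0.5: 58/29/19/14/11

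**Step 2: direction of the effect.** Read as reductions, the rows are 1 − 1/1.10 = 9.1%, 1 − 1/1.15 = 13.0%, 1 − 1/1.20 = 16.7%, 1 − 1/1.25 = 20.0% and 1 − 1/1.30 = 23.1%.

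For a true 25% reduction from 1.0 to 0.75 with SD 20% of each mean, the SD of the difference is √(0.04 + 0.0225 − 2·0.1·0.2·0.15) = √0.0565 = 0.2377, so d = 1.052. This needs 12 at 0.05 or 14 at 0.025. At 0.025 the power is 97% with 18 evaluable and 96% with 17.

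The same formula for all five rows (treated mean = 1 minus the effect, SD 20% of each mean) gives 71/31/18/12/9 at 0.05 and 84/37/21/14/11 at 0.025.

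If the SD stays at 0.2 in both conditions, the SD of the difference is √0.072 = 0.2683. At 0.025 the needs are then 92/43/25/17/13. For the 25% row the power is 92% with 18 evaluable and 90% with 17.

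**Step 3: dropout.** The printed column is n × 1.2 rounded up, for example 86 × 1.2 = 103.2, so 104. To keep n after a 20% loss requires n/0.8, which is 108/53/33/23/18. A 20% loss from the printed totals leaves 83/40/25/17/13 whole patients. On the table's own assumptions, power at 0.05 is then 89.1/89.2/89.9/88.9/88.9%.

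**The case against.** **The two alphas can be reconciled.** In the exploratory phase, 0.025 per endpoint and 5% overall could be a coherent split. That explains why both figures appear, but the table should then have used 0.025. Alternatively, 0.025 may have meant each tail of a 5% two-sided test, which would give exactly the printed sizes. The text, however, calls it the level of two-sided testing and ties it to two primary endpoints. Neither reading explains the main-trial list, which has one primary endpoint.

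**A reader might infer that the exploratory phase is underpowered.** The documents do not support this. About 84% holds only if the table's upward means are kept. For the reduction that the plan describes, the direction slip more than offsets the alpha slip in every row when the SD is 20% of each mean. With a constant SD of 0.2, the chosen 25% row still reaches 90%, although the 10% and 15% rows fall slightly short (92 and 43 needed against 86 and 42 printed). Even on the table's own means, power at 0.025 is 91.6% if all 22 complete and 81.0% if 17 do.

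**A reader might infer a familywise error near 10%, or no final significance threshold.** Neither follows. No section plans two uncorrected primary tests at 0.05: calcium is secondary in the main trial, and section 3.1 provides for multiplicity correction. Section 3.1 also gives one analysis rule, and 0.025 appears only among sample-size inputs. What is open is the alpha for the recalculation.

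**A reader might call the dropout column an arithmetic error.** It follows the plan's own rule of adding 20% of the calculated size, and 22 − 4 = 18 is what section 2.3.1 intends. The rule merely falls slightly short of a true 20% loss.

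**Table 1 does not fix the main-trial size.** This stands. The size is to be recalculated from exploratory data, and that is why the alpha in section 2.3.2 has to be settled first.

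**Conclusion.** The point stands as an error in the printed calculation and an inconsistency in the instructions for the next one. Table 1 was computed at two-sided 0.05 while the text states 0.025. On the table's own means, SDs and r = 0.1, 0.025 needs between 3 and 16 more patients per row, and the printed sizes have 83.7% to 84.6% power. Section 2.3.2 repeats both alphas for a trial with a single primary endpoint that section 3.1 tests at 0.05.

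The effect labels are also wrong for a reduction, in the conservative direction. The practical harm to the exploratory phase is therefore small: the 22 enrolled suffice at 0.025 for a true 25% reduction, provided the assumed SD of 20% and correlation of 0.1 hold. The dropout shortfall is minor, at 1 or 2 patients in four rows and 4 in the 10% row.

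**What to change.** 1. **Main trial (section 2.3.2).** State one primary endpoint (oxalate) and two-sided alpha 0.05, and delete 0.025. This agrees with sections 2.5.3 and 3.1. Do it before the recalculation in work package 3.
2. **Exploratory phase (section 2.3.1).** Either state alpha 0.05, which matches the printed sizes, and remove the two-endpoint justification for 0.025; or keep 0.025 and give the power as about 84% under the table's present assumptions.
3. **Table 1.** Re-run it at the chosen alpha with baseline 1.0 and treated = 1 minus the effect, and say whether the SD is constant or 20% of each mean. This replaces every entry and any power figure tied to the old rows. The planned 22 can stay.
4. **Abstract.** Update the 17 to 104 range. With SD 20% of each mean and alpha 0.05 it becomes 11 to 86 under the add-20% rule (9 × 1.2 = 10.8; 71 × 1.2 = 85.2), or 12 to 89 with n/0.8 (9/0.8 = 11.25; 71/0.8 = 88.75).
5. **Dropout (minor).** Inflate by n/0.8, or state that adding 20% leaves a small shortfall.

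The cost is restated figures and one rerun of the table, with no extra patients.
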